#### b. Planned Evaluations

##### *Baseline Data Analysis*

At baseline parametric and non-parametric estimates of differences will be calculated between participants pre- and post-intervention to examine differences in assessment score. Differences will be adjusted using multivariate and logistic regression models constructed to include age, gender, specialty training, facility capabilities, clinical volume, practice size, and other practice characteristics, and by patient characteristics such as type of payers. Non-parametric estimates of differences in care utilization will be calculated and adjusted for provider, practice and patient characteristics described above.

Summary tables for each group will be generated for the following:

- Practice setting (private, community, etc.)
- Practice size
- Average weekly hours in practice
- Percent of patients covered by
  - Medicare
  - Commercial/Private
  - Medicaid
  - Self-pay / Uninsured
  - Other
- Mean (+/- 2 SD)
  - Years in practice
  - Weekly hours in practice
  - Age
  - Number of hours of training in the last 12 months

##### *Longitudinal Data Analysis*

Primary Outcome Variables:

- Baseline variation in care among providers using standard of care tools, as measured by CPV® patient simulations
- In the intervention group, change in the overall and the diagnostic and treatment evidence-based quality scores and reductions in variation when caring for the CPV® simulated patient with the introduction of CDMT testing.

|             |                                                                                                                                                |                       |
|-------------|------------------------------------------------------------------------------------------------------------------------------------------------|-----------------------|
|             | Clinical Study Protocol                                                                                                                 |                       |
|             | Title: Measuring the Clinical Utility of Aegis’s Chronic Disease Management Test among VillageMD Providers: A CPV® Randomized Controlled Trial |                       |
| Supersedes: | Document Number:                                                                                                                               |                       |
|             | Effective Date:                                                                                                                                | Page: 22 of 25 |

- Changes in evidence-based management medication decisions (treatment) based on patient’s CDMT result.
- Distinguishing between medication non-adherence, DDI, and full compliance with suboptimal medication treatment (inadequate dosing vs. ineffective medication).
- Change in cost of chronic disease-related care. (This cost is modeled in part by measuring differential rates of work up/interventions/levels of care selected by each arm and multiplying by average Medicare reimbursement rates for these workups/interventions/ levels of care, and/or by modeling the incidence of expected complications and calculating associated costs per above).
- Difference in the above cost and clinical quality metrics and cost measures by three different use case types.

Secondary Outcome Variables:

- Calculation of the change in the expected cost and clinical quality metrics for each type simulated patient case (use case).

Main Explanatory Variable:

- Intervention status (exposure to intervention)

We will control for all potential confounders, including:

- Age
- Gender
- Years in practice
- Practice location
- Type of location (urban/suburban vs. rural)
- Weekly hours in clinical practice
- Number of providers in practice
- Avg. type of coverage of patients (Medicare, Medicaid, commercial, etc.)
- Participation in care quality incentive programs
- Percentage of patients that have chronic cardiometabolic disease

We will model CPV® scores as a continuous outcome variable in a multiple linear regression model, which controls for all potential confounders listed above.

Our regression model is as follows, where CPV® is the score for each provider and INTERV indicates intervention group and CASE indicates the order in which the provider took the case (first, second, third, fourth).

|             |                                                                                                                                                |                       |
|-------------|------------------------------------------------------------------------------------------------------------------------------------------------|-----------------------|
|             | Clinical Study Protocol                                                                                                                 |                       |
|             | Title: Measuring the Clinical Utility of Aegis’s Chronic Disease Management Test among VillageMD Providers: A CPV® Randomized Controlled Trial |                       |
| Supersedes: | Document Number:                                                                                                                               |                       |
|             | Effective Date:                                                                                                                                | Page: 23 of 25 |

$$Y_{it} = \text{CPV}^{\circledR} \text{ score of provider } i, \text{ at time } t$$

$$Y_{it} \sim \text{Normal}(\mu_{ijt}, \sigma^2)$$

$$\mu_{ijt} = \beta_0 + \beta_1 \text{CASE} + \beta_2 \text{INTERV} + \beta_3 \text{CASE} \times \text{INTERV} + \text{provider-practice variables}$$

For binary outcome variables, we will use a logistic regression model. Our regression is as follows, where INTERV indicates intervention group and TIME indicates time period (by week). For outcomes with a Poisson distribution, the distributional assumption would be changed from

Bernoulli to Poisson and the link would be changed from logit to log. Otherwise, the basic modeling and analysis strategy will remain the same.

$$Y_{it} = \text{appropriate therapy } t, \text{ provider } i$$

$$p_{it} = \text{probability of an outcome for time } t, \text{ provider } i$$

$$\text{logit}(E[Y_{it}]) = \beta_0 + \beta_1 \text{CASE} + \beta_2 \text{INTERV} + \beta_3 \text{TIME} \times \text{INTERV} + \text{provider-practice variables}$$

For count outcome variables we will use log linear regression (i.e., using a log link in the analysis). Cluster re-sampled bootstrapping will be used to check model distributional assumptions.

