### 3.1 Outcome Measures

- Baseline levels of variation in the work-up, recognition, and management of medication non-adherence and/or DDI in patients with more than one chronic cardiometabolic conditions and associated polypharmacy among all participants.
- Pre- and post-difference in the overall and the work-up, recognition and management quality scores between control providers using standard of care diagnostic tools and intervention providers with access to CDMT results.
- Differences in evidence-based decisions, particularly prescribing decisions, made by intervention providers and control providers, while controlling for provider and practice characteristics, between rounds 1 and 2.
- Distinguishing between medication non-adherence, DDI, and full compliance with suboptimal medication treatment (inadequate dosing vs. ineffective medication).
- Difference in expected cost of care between control and intervention providers (Cost will be calculated by measuring differential rates of medical interventions/levels of care selected by each arm, and multiplying by Medicare reimbursement rates for these interventions, and/or by modeling the incidence of expected complications and calculating associated costs per above).
- Difference in the above cost and clinical quality metrics and cost measures by three different use case types.

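### Section 8.b words the quality-score primary outcome as a one-arm change, contradicting Section 3.1 and the synopsis, and no single between-arm test of one score is designated primary

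*Protocol*

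**What the plan says.** Under Longitudinal Data Analysis, Protocol Section 8.b gives six primary outcome bullets and does not rank them:

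1. "Baseline variation in care among providers using standard of care tools, as measured by CPV® patient simulations"
2. "In the intervention group, change in the overall and the diagnostic and treatment evidence-based quality scores and reductions in variation", with the introduction of the test
3. "Changes in evidence-based management medication decisions (treatment) based on patient’s CDMT result"
4. "Distinguishing between medication non-adherence, DDI, and full compliance with suboptimal medication treatment (inadequate dosing vs. ineffective medication" (the closing bracket follows)
5. "Change in cost of chronic disease-related care", with a note that it is modelled partly from rates in each arm
6. "Difference in the above cost and clinical quality metrics and cost measures by three different use case types"

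The only secondary outcome is "Calculation of the change in the expected cost and clinical quality metrics for each type simulated patient case (use case" (closing bracket omitted).

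Section 3.1 defines the quality-score outcome differently, as a pre-post difference in "quality scores between control providers using standard of care diagnostic tools and intervention providers with access to CDMT results". The synopsis (Data Analysis) plans a comparison of intervention with control by a difference-in-difference fixed effects analysis of CPV scores. Section 8.b names intervention status as the main explanatory variable and gives a linear model with CASE, INTERV and their interaction, where CASE is the order in which cases were taken, listed as first to fourth.

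**The concern.** The second primary bullet and Section 3.1 define different quantities. One is how much intervention providers changed; the other is how much more they changed than controls. Only the second uses the randomisation. An analyst who followed the bullet literally could report an improvement that the control arm also shows.

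The list does not settle the matter in another way. It ranks nothing, combines several scores in one bullet, includes an item with no arm contrast, and places the use-case results at two levels. A reader of the final report could not tell from this protocol which result was meant to decide the trial.

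**Working it through.** **Passages side by side**

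| Place | Quantity | Control arm used? |
|---|---|---|
| Section 8.b, primary bullet 2 | Change in quality scores and variation within the intervention group | No, as worded |
| Section 3.1, second measure | Pre-post difference in quality scores, control against intervention | Yes |
| Synopsis, Data Analysis | Difference in difference on CPV scores | Yes |
| Section 8.b, main explanatory variable and linear model | Arm, and case order by arm | Yes |

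The score sets differ too. Section 8.b names overall, diagnostic and treatment scores; Section 3.1 names overall, work-up, recognition and management scores.

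**Does anything identify one primary test?**

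- The six primary bullets are not ranked. Bullet 1 is measured before the intervention and has no arm contrast. Bullet 3 depends on the test result, which only intervention providers receive, and no control counterpart is stated.
- Bullet 6 and the only secondary outcome both cover cost and quality by use case. If the secondary item was meant for the nine individual cases rather than three types, the text does not say so.
- The linear model does not say which coefficient is tested. It has no round term, and its case order stops at four although the design has two rounds of three, so six cases per provider.
- The sample size section names no outcome. Its attrition step can be followed (83 × 0.9 = 74.7, about 75 per arm) but does not point to a primary score.

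**What a one-arm change estimates**

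Let τ be the intervention effect and δ any shift from round 1 to round 2 that would occur in either arm.

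- Expected change, intervention arm: τ + δ
- Expected change, control arm: δ
- Difference between arms: (τ + δ) − δ = τ

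The one-arm change is therefore off by exactly δ.

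**Size, as an illustration**

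Input from the protocol: n = 75 per arm. Assumptions not in the protocol: two-sided level 0.05, no intervention effect (τ = 0), and drift d from 0 to 0.3 in SD units of the change score. By normal approximation, with √75 = 8.660:

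P(significant) = 1 − Φ(1.96 − d√75) + Φ(−1.96 − d√75)

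| d | d√75 | P(significant one-arm change) |
|---|---|---|
| 0 | 0 | 5% |
| 0.1 | 0.866 | 14% |
| 0.2 | 1.732 | 41% |
| 0.3 | 2.598 | 74% |

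A between-arm test stays at 5% in every row when the drift is the same in both arms, because δ cancels.

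**The case against.** The strongest reply is that the randomised comparison is plainly there: in the synopsis, in Section 3.1, and under the same heading as the disputed bullet, where arm is the main explanatory variable. An effect of arm cannot be estimated from one arm. Hypothesis 6 of Section 8.a also compares with control providers, and the cost bullet refers to each arm. This stands. A reader might infer that the trial has no randomised comparison, or that its reported effect will be biased. The documents support neither; the stated models would estimate a contrast between arms.

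A second reply is that the protocol calls learning effects small and randomises case order to cancel them. Random order balances cases within a round, and random assignment of cases argues against a systematic difference in case difficulty between rounds. It cannot remove drift between rounds, because round 2 always follows round 1. Small drift does make the bias small, which is why the illustration starts at zero.

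A third reply is that an SAP may settle multiplicity. That is fair. A reader might go on to compute an inflated false-positive rate for the list. The protocol gives no significance level, the scores come from the same vignettes and are unlikely to be independent, the number of tests depends on how the bullets are read, and a testing procedure may exist in a plan not shown. No such rate is claimed here. An SAP does not, however, cure a protocol that defines one outcome in two ways and places another at two levels.

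**Conclusion.** The point holds as an inconsistency in how the primary outcome is defined. Bullet 2 contradicts Section 3.1, the synopsis and the model in its own section. A between-arm analysis is described, but it is not labelled primary or tied to one score or one coefficient. It would go too far to call the one-arm item the main primary outcome, since the protocol ranks none of the six.

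Taken literally, the one-arm wording carries a bias equal to the drift between rounds. The 14% to 74% range rests on the assumed level, the assumed drift and a true effect of zero. It shows how quickly drift matters at 75 providers and does not predict this trial's result. The contradiction and the missing designation do not depend on those assumptions.

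**What to change.** - In Section 8.b, reword bullet 2 as the between-arm difference in change, round 2 minus round 1.
- Designate one score as the single primary outcome, for example the overall CPV score. Which score is the sponsor's choice, but there should be one, and the score names should match Section 3.1.
- Present baseline variation as descriptive.
- Move domain scores, variation, medication decisions, distinguishing of causes, and cost to secondary.
- List the use-case results once, as secondary, and say whether they are by three types or nine cases.
- State which model coefficient is the primary test and make it match the difference-in-difference in the synopsis. This needs a round term, or an explanation of how case order stands in for one.

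The multiplicity procedure can stay with the SAP. The cost is re-labelling and a short change to the model text, best made before any comparison between arms is seen. The downside is that fewer results can be called primary.

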After receiving the CDMT education materials, intervention group providers will be asked to complete another set of CPVs®, this time, they'll be able to access the CDMT and its results and use it to diagnose and treat their patient. Control group providers will neither access the CDMT educational material nor be able to use its results in their routine care for their simulated patient.

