## 2.2 Study Interventions

Intervention-arm providers will receive two interventions:

- Educational materials
  - All intervention group providers will first receive educational materials (e.g., a slide deck, webinar, fact sheet and/or case studies) on the CDMT.
- CDMT results
  - All intervention group providers will receive CDMT results at the appropriate point in each of the round 2 CPV® cases whether they select it or not.

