## 8. STATISTICAL ANALYSIS

### a. Study Hypotheses

1. Provider participants at baseline will not recognize that patients do not meet therapeutic goals due to medication non-adherence and show high levels of unwarranted variation in their work-up, recognition, and management of medication non-adherence in patients with more than one chronic cardiometabolic conditions and associated polypharmacy using in the CPV® patient simulations.
2. Providers will not recognize that patients do not meet therapeutic goals due to DDI and show high levels of unwarranted variation in their work-up, recognition, and management of medication non-adherence in patients with more than one chronic cardiometabolic conditions and associated polypharmacy using in the CPV® patient simulations.
3. The intervention group, those who receive educational materials about the CDMT and CDMT results in their round 2 patient, will improve their quality of care and have less practice variation when caring for their CPV® patients with more than one chronic cardiometabolic conditions and associated polypharmacy, as measured by management decisions to recognize and/or manage medication non-adherence, DDI, and associated co-morbidities.
4. The additional information from the CDMT will result in better distinction between medication non-adherence and DDI and lead to better overall care including reduction in over-use of invasive diagnostic work-up and treatment, and a reduction in cost in a subset of patients. The associated cost savings, particularly for those patients will come from obviating high-cost workup, avoidance of unneeded subspecialty referrals, increased diagnosis and treatment of drug-drug interactions and/or reducing the frequency or number of medical interventions ordered.
5. Of the nine simulated cases that will focus on patients with multiple chronic cardiometabolic conditions and polypharmacy, there will be a subset of use cases where the CDMT demonstrates greater utility.
6. Providers with access to the education materials and CDMT will diagnose

|             |                                                                                                                                                |                       |
|-------------|------------------------------------------------------------------------------------------------------------------------------------------------|-----------------------|

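### The cost outcome is triggered by care that providers select, but the CDMT is supplied whether selected or not, so a supplied but unselected test is not charged on a literal reading

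*Protocol*

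**What the plan says.** The protocol defines the cost outcome in three places.

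- Section 8.b, under the primary outcome variables, models cost *in part* by "measuring differential rates of work up/interventions/levels of care selected by each arm and multiplying by average Medicare reimbursement rates".
- Section 3.1: "Cost will be calculated by measuring differential rates of medical interventions/levels of care selected by each arm", multiplied by Medicare rates. The Synopsis (Outcome Measures) uses the same rule.
- All three add a second branch: "and/or by modeling the incidence of expected complications and calculating associated costs per above".

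Section 2.2 says that intervention providers "will receive CDMT results at the appropriate point in each of the round 2 CPV® cases whether they select it or not". The Synopsis (Study Interventions) and Sections 2.1 and 6.3 say the same. On the other arm, Section 2 says: "Control group providers will neither access the CDMT educational material nor be able to use its results".

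The cost hypothesis in Section 8.a expects "a reduction in cost in a subset of patients". The sources of saving that it names all lie downstream of the test, such as "obviating high-cost workup, avoidance of unneeded subspecialty referrals". No offset for the test itself is named. The protocol does not price the CDMT. It says neither that the test is charged to the intervention arm nor that it is left out.

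**The concern.** Exposure to the test is universal in round 2 of the intervention arm, but the trigger for costing is selection. Two intervention providers who see the same CDMT result and then manage the case identically can be given different costs, only because one ordered the test and the other did not. The arm is credited with every downstream effect of the supplied result. Read literally, it pays for that result only where a provider happened to select it.

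Objective 3 asks whether receiving results leads to higher-value or lower-cost decisions, and Section 1 presents studies of this kind as evidence for payers. A payer would take a reported saving to be net of the test. The hypothesised saving is confined to a subset of patients, and cost is also compared by use case. Where the gross saving is modest, an uncharged test could change the sign of the difference.

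**Working it through.** **The plan's own figures.** The Synopsis (Sample Size) gives 83 recruited per arm, 10% attrition and 75 expected per arm. 83 × 0.9 = 74.7, so the stated 75 is reproduced. Section 2.1 gives three cases per round. Round 2 intervention cases: 75 × 3 = 225. There is no stated cost figure to reproduce.

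**Is a supplied but unselected test charged under any reading of the two branches?**

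- Selected care × Medicare rates: no, because the test was not selected. A test that was selected could be priced as *work up*, a term that appears only in Section 8.b. Section 3.1 and the Synopsis do not use it.
- Modelled complications: no. This branch covers complications, not the test.
- Both together: no, since neither part charges it.

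**Size.** Let C be the price of one CDMT and s the share of round 2 intervention cases in which the test is selected and priced. Then:

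- amount that should be charged per case = C
- amount charged under the literal rule = C × s
- understatement per case = C × (1 − s)

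Controls never receive the test and nobody receives it in round 1. The understatement therefore falls only on the intervention arm in round 2, and it passes in full into the difference-in-difference comparison. Its sign is fixed: it is zero or it favours the CDMT.

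**Illustration.** Neither C nor s is in the protocol. The prices below are assumptions chosen to show a range.

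| Assumed price C | s = 0 | s = 0.5 | s = 1 |
|---|---|---|---|
| $100 | $100 | $50 | $0 |
| $250 | $250 | $125 | $0 |
| $500 | $500 | $250 | $0 |

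Entries are the understatement per case.

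**Effect on the sign.** Suppose a gross downstream saving of $150 per case (also an assumption) and s = 0. The rule would report $150. Net of the test it would be:

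- 150 − 100 = +$50
- 150 − 250 = −$100
- 150 − 500 = −$350

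The break-even price equals the gross downstream saving per case, here $150.

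**The case against.** The strongest reply is that the protocol nowhere excludes the test's price. Section 8.b says that cost is modelled only *in part* from selected care, and it includes work-up. The CDMT is a diagnostic test that intervention providers appear able to select, so a selected CDMT can be priced, and with full selection nothing is omitted. This stands. A reader might infer that cost counts only selected care, or that the price is definitely left out. The text supports neither inference.

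A second reply is that unit costs, and the choice between costing branches, commonly sit in a statistical analysis plan, which is not shown here. This stands for the price itself and for the choice between branches. A reader might infer from the *and/or* that the costing method will be picked after the data are seen. The protocol does not say so, an analysis plan could settle it, and the wording also allows both branches to be used. The reply does not remove the point made here, which concerns a rule that the protocol itself states. Costing is tied to selection while delivery is not, and an analysis plan that follows the rule inherits the mismatch.

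A third reply is that the downstream cost of providers' decisions is a coherent quantity, and that Objective 3 is worded around decisions. That is fair, and such an outcome is acceptable if it is labelled as excluding the test. The present definitions carry no such label, and the objective also refers to decisions expected to lower overall costs.

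**Conclusion.** The point holds in a limited form. As defined, the cost outcome does not ensure that every supplied CDMT is charged. On a literal reading it leaves the test uncharged wherever it was supplied but not selected. The resulting understatement is C × (1 − s) per round 2 intervention case, between zero and the full test price, over 225 cases at the expected number of completers. Any omission favours the CDMT.

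The direction follows from the design alone. The size does not: it depends on a price and a selection share that the protocol does not give, and the dollar figures above are illustrations. The protocol therefore does not show that the saving is overstated by any particular amount, or that a real saving would reverse. The point bears on the cost outcome and the cost comparison by use case, and leaves the quality-score outcomes untouched.

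**What to change.** In the Synopsis (Outcome Measures), Section 3.1 and Section 8.b, state that one CDMT is charged to every round 2 intervention case, selected or not, and that a selected CDMT is not counted a second time as work-up.

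Report both the gross (downstream) and the net cost difference, the latter over a stated range of test prices. Label any result without the test price as downstream cost excluding the test, and give the break-even price with it.

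Align the three definitions, since *in part* and *work up* appear only in Section 8.b.

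The cost is a short wording change in three places and a simple added calculation, with no new data. A test price has to be stated or assumed, and the reported net saving will be less favourable than one that leaves supplied tests uncharged.
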